### Statistical analysis

We will describe psychiatrist and claimant characteristics with absolute and relative frequencies for categorical variables and with mean and standard deviation, or median and interquartile range, for continuous variables. To explore whether random allocation of psychiatrists to claimants was successful, i.e., producing low rater-group-membership, we will calculate the frequency of the same two, three or four psychiatrists being allocated to a claimant (‘rater-group-membership’) and calculate the Jaccard similarity coefficient of each pair of psychiatrists.

Each rating (rather than a consensus rating) will be used for our analysis. To estimate the means and associated 95 % CIs for the primary and secondary outcomes we will use mixed-effects models that take into account the crossed cluster design (i.e., each psychiatrist will assess several claimants and each claimant will be assessed by several psychiatrists) by including crossed random intercepts for claimants and psychiatrists, if appropriate, in order to obtain adjusted standard errors [46].

Furthermore, we will use mixed-effects models to estimate the variance components needed for the computation of the ICCs of work capacity, IFAP items and IFAP item sums (i.e., the residual variance and between-claimant variance for the ICC_absolute agreement_, and additionally between-psychiatrist variance for the ICC_consistency_) [47]. The associated measures of precision (95 % CIs) will be obtained by model-based parametric bootstrapping. Additionally, we will perform exploratory subgroup analyses on the ICCs for work capacity for specific diagnostic groups (ICD 10 categories of mental disorders, F00-F09; F10-F19; F20-F29; F30-F39; F40-F48; F50-F59; F60-F69). The clinical interpretation of ICC and agreement will follow the criteria by Fleiss [48] and Cicchetti [49]. For the ICC: poor (ICC < 0.4); fair (0.40 to 0.59); good (0.60 to 0.74); excellent (0.75 to 1.00), for the level of percentage agreement: poor (<70 %); fair (70 % to 79); good (80 to 89 %); excellent (>90 %).

To assess the associations of certain claimant traits (age, gender, IFAP 2 scores) and psychiatrist judgments (severity of disease, certainty of rating) with the reliability of work capacity, we will use a likelihood ratio test to compare two mixed-effects models, with one model allowing for heteroscedasticity between the claimant groups as specified by the claimant trait or psychiatrist judgment of interest. We will compute ANOVAs of mixed-effects models with main diagnosis or severity as a fixed effect to assess differences in certainty in work capacity ratings between main diagnoses or severity of disease. To check for a rater effect with regard to work capacity, where some psychiatrists may be systematically more lenient or strict in their judgments, we will use a likelihood ratio test to compare the two corresponding mixed-effects models used for the computation of ICC_absolute agreement_ and ICC_consistency_.

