### Procedures

#### The interview

The assessment centers will assign all enrolled study claimants to the next available study psychiatrist. Following a review of the claimants’ medical records provided by the insurer, experts will use the functional evaluation technique [26] to interview claimants. Interviews are anticipated to last 2 to 3 h, and will take place at an assessment center or the psychiatrist’s office.

The same research assistant will record all videos to ensure standardized recordings, using two cameras to prevent technical failures. Claimants will be filmed, but the assessing psychiatrist will remain off camera. The interviewing experts will write a psychiatric evaluation report for the insurer which will be integrated in the final polydisciplinary report. Psychiatrists who conduct the evaluation interview will provide a summary of the claimant’s socio-medical history for the rating psychiatrists who will review the video of the evaluation and complete study forms as detailed below.

Following the interview, and in the absence of the expert, the research assistant will provide the Questionnaire on Perceived Fairness to all claimants, with instructions that they can complete and return the form immediately, or later at home and return it to the research center in a sealed envelope.

The ratings: Three psychiatrist raters from a pool of 20 raters will be randomly allocated, via a web application, to each enrolled claimant. Randomization will prevent selection bias (e.g., the same three raters consistently forming a group [‘rater-group-membership’]) [37]. To avoid contamination, raters will be blinded to co-raters who view the same videotape [38, 39]. Four ratings will be generated for each enrolled claimant: one by their interviewing psychiatrist and three by psychiatrists who will independently review the video of the evaluation.

Psychiatrist raters will review videos of claimants’ evaluation interviews, their medical histories and job descriptions, and complete the IFAP-instruments through a secured website. All psychiatrists will receive information on how to access the secured website and standby support from the research team in case of unforeseen challenges with the data-security system.

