### Sample size

Our primary outcome is psychiatrists’ global rating of work capacity (expressed as percentage work capacity) in the previous job and in suitable alternative work. The intra-class correlation coefficient (ICC) should be at least 0.6 to be useful [42], which seems achievable in the insurance medicine context. [43, 44] With a sample size of 30 claimants, each evaluated by four raters, we expect to estimate an assumed ICC of at least 0.6 with a precision expressed as the width of a two sided 95 % confidence interval (CI) of ± 0.15 [45].

In an exploratory analysis, we will assess which variables – clinical (diagnoses), professional (psychiatrists’ characteristics) and demographic (claimants’ characteristics) – are associated with variation in the reliability of expert judgments, although we anticipate that these analyses will be underpowered to detect significant associations.

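### The variance components listed for the two ICCs give either a mislabelled agreement coefficient or, on the more likely two-model reading, a confidence interval that is too narrow when psychiatrists differ in leniency

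*Protocol article*

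**What the plan says.** All references are to the protocol article.

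- **Statistical analysis, components.** Mixed-effects models supply the variance components for the ICCs, given as "the residual variance and between-claimant variance for the ICC_absolute agreement_, and additionally between-psychiatrist variance for the ICC_consistency". No ICC formula is printed. The 95% intervals come from model-based parametric bootstrapping.
- **Statistical analysis, rater effect.** The stated aim is "To check for a rater effect with regard to work capacity, where some psychiatrists may be systematically more lenient or strict in their judgments". The method is a likelihood ratio test to "compare the two corresponding mixed-effects models used for the computation of ICC_absolute agreement_ and ICC_consistency".
- **Statistical analysis, means.** For the outcome means, the crossed design is handled "by including crossed random intercepts for claimants and psychiatrists, if appropriate, in order to obtain adjusted standard errors". The ICCs follow in a separate paragraph.
- **Sample size.** "The intra-class correlation coefficient (ICC) should be at least 0.6 to be useful"; the type of ICC is not named. The precision statement begins "With a sample size of 30 claimants, each evaluated by four raters" and claims a "precision expressed as the width of a two sided 95 % confidence interval (CI) of ± 0.15".
- **Procedures, The interview.** "Three psychiatrist raters from a pool of 20 raters will be randomly allocated, via a web application, to each enrolled claimant". The interviewing psychiatrist gives the fourth rating.

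**The concern.** In a crossed model with claimant variance Vc, psychiatrist variance Vp and residual variance Ve, Vp belongs in the denominator of the agreement ICC and is absent from the consistency ICC. The article attaches Vp to consistency and leaves it out of agreement. It also does not say which of the two coefficients is compared with 0.6.

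The work capacity percentage is used to calculate benefits, so a systematic difference in strictness between experts is disagreement that the study has to count. The abstract and the conclusion also tie the decision to go on to a randomized trial to finding moderate reliability. Both the coefficient called agreement and its interval therefore need to reflect psychiatrist variance properly.

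**Working it through.** **Inputs.** The Sample size section gives n = 30 claimants, k = 4 ratings and an ICC of 0.60. The interview section gives 20 psychiatrists. There are 30 × 4 = 120 ratings, so 120 / 20 = 6 per psychiatrist on average. The article gives no variance shares; those below are assumptions, with total variance set to 1.

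**The plan's own precision figure.** The large-sample half-width is 1.96 × √[2(1 − r)²(1 + (k − 1)r)² / (k(k − 1)(n − 1))]. At r = 0.60 this is 1.96 × √[2 × 0.16 × 7.84 / (12 × 29)] = 0.166. The F-based interval at an observed 0.60 runs from 0.430 to 0.756, a half-width of 0.163. The stated ± 0.15 is not reproduced at 0.60; it is reached at an ICC of about 0.65 to 0.66. That is a separate matter. What counts here is that these formulas are one-way and contain no psychiatrist term.

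**Reading 1: both ICCs from one crossed model.**

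- Agreement = Vc / (Vc + Vp + Ve)
- Consistency = Vc / (Vc + Ve)

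If Vc and Ve alone are used for the coefficient labelled agreement:

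| Vc / Vp / Ve | True agreement | Reported as agreement |
|---|---|---|
| 0.60 / 0.10 / 0.30 | 0.600 | 0.60 / 0.90 = 0.667 |
| 0.50 / 0.20 / 0.30 | 0.500 | 0.50 / 0.80 = 0.625 |
| 0.50 / 0.25 / 0.25 | 0.500 | 0.50 / 0.75 = 0.667 |

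**Reading 2: two nested models.** A likelihood ratio test for a rater effect needs one model with a psychiatrist term and one without. By the component list, the agreement model is the one without. Its residual is then Ve* = Vp + Ve, and Vc / (Vc + Ve*) is a one-way absolute-agreement ICC. In simulation (30 claimants, 4 of 20 raters each, 150 runs per row), the mean estimates were:

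| Vc / Vp / Ve | Claimant-only model | Crossed-model agreement |
|---|---|---|
| 0.60 / 0.10 / 0.30 | 0.592 | 0.595 |
| 0.50 / 0.20 / 0.30 | 0.490 | 0.495 |
| 0.50 / 0.25 / 0.25 | 0.490 | 0.496 |

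The point estimate is not materially affected.

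**The interval under reading 2.** A bootstrap from the claimant-only model draws ratings that are independent given the claimant, whereas real ratings by the same psychiatrist share that psychiatrist's leniency. Simulating the design at a true agreement ICC of 0.60, with four psychiatrists drawn at random per claimant, and applying the one-way F interval as a stand-in gives:

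| Assumed Vp share | Coverage of the 95% interval | Mean half-width | Actual half-range of the middle 95% of estimates |
|---|---|---|---|
| 0% | 95.2% | – | – |
| 10% | 94.4% | 0.162 | 0.173 |
| 20% | 92.5% | 0.162 | 0.186 |
| 30% | 89.6% | 0.162 | 0.202 |

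The mean estimate is about 0.588 at every share. The interval keeps its width while the true spread grows.

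The percentile bootstrap behaves the same way. It covers 94.3% with no rater effect. The claimant-only version then covers 93.4%, about 92% and 89% at shares of 10%, 20% and 30%; the crossed-model version covers 94.0%, about 96% and 95.5%.

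**The case against.** The strongest reply is that the article does not describe a single crossed model for both ICCs. The rater-effect test refers to two models, and under that scheme the labels are defensible: the agreement model leaves leniency in the residual, and the consistency model takes it out. A reader might infer from the component list alone that the labels are simply reversed and that a true agreement of 0.50 will be reported as 0.625 and pass 0.6. The documents do not support that. It requires reading 1, no denominator is printed, and reading 2 shows no inflation. This part of the reply stands.

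A reader might also see a contradiction with the crossed intercepts in the same section. Those are specified for the outcome means, and only where appropriate, so a claimant-only model for one ICC does not strictly contradict them. This stands too.

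It can further be said that joint training and calibration aim to keep rater differences small, that the loss at 10% is negligible, that the rater effect is tested openly, and that exact formulas are often left to an analysis plan. All fair, but they do not dispose of the interval. The article itself fixes the component assignment and the bootstrap method, and it expects that some psychiatrists may be stricter than others. Following its text gives an interval that is correct only if they are not.

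The consistency wording also remains loose. Psychiatrist variance must be fitted so that it leaves the residual, but it is not a term of that coefficient. An analyst who puts it in the denominator would obtain agreement from both models and no consistency ICC.

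**Conclusion.** The concern holds in a limited form. The component list is ambiguous: one reading mislabels the coefficient, while the other, better supported by the article, gives a sound point estimate with an interval that is too narrow whenever psychiatrists differ in leniency. On that second reading, nominal 95% coverage falls to about 94%, 92.5% and 90% at rater shares of 10%, 20% and 30%.

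These figures rest on assumed shares, a true ICC of 0.60, normally distributed effects, and all four raters drawn at random from 20. In the study the interviewer is the next available psychiatrist, not a random draw. The inflated values under reading 1 show what a misreading could do; they are not an expected result. The missing link between the 0.6 target and a named coefficient adds to the ambiguity: with shares of 0.50 / 0.20 / 0.30, agreement (0.500) and consistency (0.625) fall on opposite sides of it. The point is worth correcting because the correction is nearly free, but it does not undermine the design.

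**What to change.** For each outcome, fit one crossed model with random claimant, random psychiatrist and residual terms. From it compute ICC_agreement = Vc / (Vc + Vp + Ve) and ICC_consistency = Vc / (Vc + Ve), and print both formulas. Run the parametric bootstrap from that model, keeping the realised allocation of psychiatrists to claimants. State that ICC_agreement is the coefficient compared with 0.6 and that consistency is supportive. Keep the claimant-only model only as the null model for the rater-effect test.

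The cost is a few sentences and a few lines of code, with no change to the data collected. The drawback is slightly wider intervals when psychiatrists differ in leniency.

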### Data collection

Sociodemographic data on all eligible claimants (age, gender, civil status, nationalities and country of origin) and psychiatric experts (age, gender) will be recorded, complemented by psychiatrists’ professional experience (years since specialization; years working as psychiatric expert; number of work capacity evaluations over the last year; working concurrently as treating psychiatrist and psychiatric expert [Yes/No]). For eligible claimants who chose not to participate, insurance staff will record their mental disorder, gender and age.

Following each disability evaluation, the interviewing psychiatrist and three psychiatric raters will record all mental disorders that impact on work capacity using ICD 10 coding. They will fill in the IFAP-instrument, thereby providing estimates and judgments on overall work capacity related to the claimants’ previous job and to suitable alternative work (single item on a scale from 100 to 0 %, higher values indicate better work capacity), and on the following variables: commonly affected mental functions (12 items on a 5-point scale, higher score indicate greater impairment) and functional capacities commonly affected in mental disorders, also related to the claimants’ previous job and to suitable alternative work (13 items on a 5-point scale, higher scores indicate greater impairment).

Each psychiatrist who completes a disability evaluation will rate their certainty regarding the claimant’s overall work capacity (scale from 0 to 10, higher scores indicate greater certainty), the severity of the claimants’ mental disorder(s) compared to that of other claimants with similar mental disorders (scale from 0 to 10, higher scores indicate greater severity), and the extent to which claimants in the study represent ‘typical claimants’ referred for disability evaluation.

Six criteria capture ‘typicality’ in the context of our study: severity of mental disorders, complexity of diagnoses, impact of the claimants’ mental disorders on work capacity, work trajectory, spectrum of jobs and occupational activities, and education and professional training. For each criterion, respondents will relate the current claimant to other claimants assessed in their practice, report the frequency of evaluating such a claimant on a 3-item scale (seldom/neither seldom nor often/often) and generate a global judgment on the frequency of encountering such a claimant (same 3-item scale).

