## Discussion

### What this study contributes

Reliability studies are often used to evaluate the measurement properties of human observers [50]. The results of this real-life study will provide an estimate of the measurement properties among expert psychiatrists who use our functional evaluation approach when determining health-related work capacity of workers claiming disabling mental illness.

Insurer’s typically consider medical evaluations as the best evidence for informing whether or not to award disability benefits [14]. However, for any evaluation process to be valid, it must first demonstrate reliability (although reliable evaluations can still be invalid). Inter-rater reliability can inform about the fairness of expert judgments (i.e., whether the claimants‘ evaluators come up with similar levels of functional impairment and similar judgments on remaining work capacity) when an independent reference standard for the diagnosis ‘work incapacity’ is lacking. Reliability reflects the extent to which medical evaluations can discriminate between claimants despite measurement errors inherent in the assessment. Reliable evaluations should consistently distinguish between claimants with high, moderate and low work capacity when performed by knowledgeable experts.

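### The planned likelihood ratio test compares variances between claimant groups, not ICCs, so its p-value does not answer the stated question about reliability

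*Protocol article*

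**What the plan says.** The Statistical analysis section of the protocol article opens this analysis with its aim: "To assess the associations of certain claimant traits (age, gender, IFAP 2 scores) and psychiatrist judgments" (the latter being "severity of disease, certainty of rating) with the reliability of work capacity"). The method follows at once: "we will use a likelihood ratio test to compare two mixed-effects models, with one model allowing for heteroscedasticity between the claimant groups". The article does not name the variance component that is allowed to differ.

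The same section measures reliability by ICCs computed from variance components: "the residual variance and between-claimant variance for the ICC_absolute agreement_, and additionally between-psychiatrist variance for the ICC_consistency". The Discussion, under What this study contributes, adds that "Reliability reflects the extent to which medical evaluations can discriminate between claimants despite measurement errors inherent in the assessment".

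ICCs by subgroup are planned for ICD-10 diagnostic groups only, not for the traits and judgments listed above. Sample size and Limitations describe analyses of this kind as exploratory, underpowered and informative about trends only, though possibly of use in planning later studies.

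**The concern.** The target and the test do not match. An ICC sets between-claimant variance against error. A test for heteroscedasticity asks whether variances are equal. Two groups can have different variances and the same ICC, or the same residual variance and very different ICCs.

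If a small p-value is read as showing that reliability depends on age, gender, severity, certainty or IFAP 2 score, that reading may be false. These results are meant to show trends for future work, so what they are trends in matters. The disclosed low power does not cover this, because low power and testing a different hypothesis are separate problems.

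**Working it through.** **Inputs.** From the article: "With a sample size of 30 claimants, each evaluated by four raters, we expect to estimate an assumed ICC of at least 0.6". The article gives no group sizes, variances or operating figures for this test, so there is no stated figure to reproduce. Assumed here: two equal groups of 15 claimants, four ratings each, 5% level, no rater effect, and group A with between-claimant/residual variance 600/400, so ICC = 600/(600 + 400) = 0.60.

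**Step 1: the two null hypotheses.** Write B_g and E_g for the between-claimant and residual variance in group g, with ICC_g = B_g/(B_g + E_g).
- Equal ICCs means B_A/E_A = B_B/E_B.
- Equal residual variances means E_A = E_B.
- If B_A = B_B, each implies the other. Otherwise they are different hypotheses.

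**Step 2: residual-variance test when the ICCs are equal.** Each group has 15 × (4 − 1) = 45 within-claimant degrees of freedom. The two-sided 5% limits of F(45, 45) are 0.553 and 1.807. If the true residual ratio is t, the rejection probability is P(F < 0.553/t) + P(F > 1.807/t).
- t = 1: 5%.
- t = 1.5, both variances 1.5 times larger, ICC 0.60 in both groups: about 27%.
- t = 2, ICC 0.60 in both groups: about 63%, and about 64% with the likelihood ratio form of the test.

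**Step 3: full mixed-model likelihood.** Simulation, 2,000 runs per row. The three tests are: residual variance free by group (1 df); both variances free by group (2 df); and a direct test of equal ICCs with both variances free (1 df).

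| Group B (between/residual) | ICC A v B | Residual free | Both free | Direct ICC test |
|---|---|---|---|---|
| 600/400 | 0.60 v 0.60 | 5.0% | 5.9% | 6.0% |
| 300/200 | 0.60 v 0.60 | 67% | 66% | 6.0% |
| 150/100 | 0.60 v 0.60 | 99.8% | 99.8% | 5.1% |
| 600/200 | 0.60 v 0.75 | 64% | 54% | 18% |
| 133/200 | 0.60 v 0.40 | 71% | 85% | 17% |
| 100/200 | 0.60 v 0.33 | 70% | 90% | 28% |
| 100/400 | 0.60 v 0.20 | 5.7% | 52% | 52% |

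Rows 2 and 3 show that neither form of the heteroscedasticity test is a test of equal reliability. Row 4, with equal between-claimant variance, is the case in which the residual test points the right way.

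**Step 4: what depends on freeing the residual variance only.** In the last row an ICC difference of 0.40 that comes from between-claimant variance is met with 5.7% rejection, in effect the nominal level. In the rows with 133/200 and 100/200, every rejection arises because B has the smaller residual, so B looks more reliable although its ICC is lower. With both variances freed, the fitted components would show the ICC direction, but the p-value would still not test it.

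**Step 5: limits of comparing group ICCs.** Power is low: 17% for 0.60 v 0.40. Splitting on a variable related to work capacity also narrows between-claimant variance. For a normal outcome split at the median of a variable with correlation r, the between-claimant variance within each half is multiplied by 1 − 2r²/π. Starting from 0.60 between and 0.40 residual:
- r = 0.5: 0.504/0.904 = 0.56.
- r = 0.7: 0.413/0.813 = 0.51.
- r = 1: 0.218/0.618 = 0.35.

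Rater error is unchanged throughout, so group ICCs partly reflect case mix.

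**The case against.** The strongest reply is that the article is a condensed document, that it does not say which variance may differ, and that the model specification may sit in a fuller plan. This stands in part. A reader might infer that the analysis has no power for real reliability differences, or that it will point the wrong way. The article does not support either as a flat statement: both need the residual-only reading, which is usual but unstated. Rejection at equal ICCs does not depend on that reading.

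A second reply is that the Discussion also describes inter-rater reliability as evaluators reaching similar judgments, which is agreement, and that residual variance measures agreement directly. This also stands. The Discussion gives no variance ratio; the ICC as the measure comes from the Statistical analysis section. A residual-variance test is a legitimate analysis of rating error if it is labelled so.

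Two further inferences should not be drawn. One is that the bounded 0–100% scale must make severity or IFAP 2 groups differ in residual variance. That depends on an assumed low mean and large spread, for which the article gives no figure, and the effect disappears with a mean near 50. The other is that certainty belongs to each rating and so cannot define claimant groups. The Data collection section says "Each psychiatrist who completes a disability evaluation will rate their certainty regarding the" claimant's work capacity, which may mean the interviewer alone and hence one value per claimant. How IFAP 2 scores are combined or cut is a detail for the analysis plan.

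Finally, the analysis is declared exploratory and underpowered. That limits the consequence but does not make the test address the stated aim.

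**Conclusion.** The point holds and is minor. The article names a target, association with reliability, and a test whose null is equal variances. The two agree only when between-claimant variance is constant across groups. At equal ICCs of 0.60, the residual-variance test rejects about 27% or 64% of the time for a variance factor of 1.5 or 2, and freeing both variances rejects about 66% of the time at a factor of 2. These sizes rest on the assumed equal split, variances and 5% level, and on no rater effect. The mismatch itself needs none of them.

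Missed ICC differences and results favouring the less reliable group are conditional on only the residual variance being freed. The primary ICC, its confidence interval and the 0.6 criterion are untouched.

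**What to change.** For each trait or judgment, fit a model in which both the between-claimant and the residual variance may differ by group. Report both variances, the group ICCs, the difference in ICCs and the standard error of measurement (the square root of the residual variance), with 95% confidence intervals from the parametric bootstrap already planned in Statistical analysis. Name the component in any variance test that is kept, and describe a test on residual variance as a test of rating error (agreement), not of reliability.

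The cost is a change of wording and some programming; no new data are needed. There are two downsides. The intervals for ICC differences will be wide. Group ICCs formed on IFAP 2 scores or severity will partly reflect restricted case mix, which is why the residual variance should stand beside them.
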